## Abstract

**Background:**

Infancy is a period of rapid growth and habit formation and hence could be a critical period for obesity prevention. Excess weight gain during infancy is associated with later obesity and formula-fed babies are more likely to gain excess weight compared to breastfed babies. The primary trial outcome is a change in the weight standard deviation score from birth to 1 year.

**Methods/Design:**

We will recruit 650 to 700 parents who introduce formula-milk feeds within 14 weeks of their baby's birth to a single (assessor) blind, parallel group, individually randomised controlled trial. The focus of the intervention is the caregiver (usually the mother), and the focus of the primary outcome is the infant. The intervention group will receive the behavioural intervention, which aims to reduce formula-milk intake, promote responsive feeding and healthy weaning, and prevent excessive weight gain during infancy. The intervention is based on Social Cognitive Theory and action planning (‘implementation intentions’). It consists of three components: (1) a motivational component to strengthen parents’ motivation to follow the *Baby Milk* feeding guidelines, (2) an action planning component to help translate motivation into action, and (3) a coping planning component to help parents deal with difficult situations. It will be delivered by trained facilitators (research nurses) over 6 months through three face-to-face contacts, two telephone contacts and written materials. The control group will have the same number of contacts with facilitators, and general issues about feeding will be discussed. Anthropometric outcomes will be measured by trained research staff, blind to group allocation, at baseline, 6 months and 12 months following standard operating procedures. Validated questionnaires will assess milk intake, temperament, appetite, sleep, maternal quality of life and maternal psychological factors. A 4-day food diary will be completed at 8 months.

**Discussion:**

The results of the trial will help to inform infant feeding guidelines and to understand the links between infant feeding, behaviour, appetite and growth.

**Trial registration:**

ISRTCN20814693. Registration date 13 January 2011.

## Background

Childhood obesity has important consequences for morbidity and mortality in childhood and in later life [1]. In 2010, 43 million children under the age of five were obese or overweight worldwide and the prevalence is predicted to rise from 6.7 % to 9.1 % in 2020 [2]. In England, data from the National Child Measurement Programme (NCMP) show that by the time children start school, more than one in five are overweight, and one in 10 are obese [3]. Hence, tackling childhood obesity through focussing on the early years has become a national priority [4]. However, to date, there is little evidence on which to develop effective strategies to prevent childhood obesity [5]. A Cochrane Review identified 22 randomised trials to prevent childhood obesity; although some diet and physical activity interventions were effective in promoting a healthy diet and increased physical activity levels, they were not on the whole effective in preventing weight gain [6]. Only one of the included studies recruited children below one year of age (average age 21 months, *n* = 43), and that was a home-visiting programme for high-risk Native-American children, focussing on improving parenting skills to develop appropriate eating and exercise behaviours to prevent obesity [7].

Infancy is a period of rapid growth and could be a critical time when obesity prevention may be most effective. Recent systematic reviews have described a consistent association between rapid weight gain in infancy and subsequent obesity risk in childhood and later life [8–10]. Energy deposition as a percentage of total energy requirements decreases from 40 % at 1 month to 1 to 2 % from 12 months until mid-adolescence. Therefore, infancy weight gain is more closely related to energy intake, than is weight gain in childhood or in later life. In 2004, based on new data on energy expenditure in infants, the World Health Organisation (WHO) reduced the recommended energy requirements for infants by 15 to 20 % [11]. Current formula-feeding instructions in UK are based on the previous 1985 WHO recommendations and this may be an important reason why formula-fed babies are at a greater risk of rapid weight gain and subsequent obesity than breastfed infants. Three meta-analyses of observational studies reported that obesity risk at school age was reduced by 15–20 % in breastfed compared with formula-fed infants [12–14]. In 2006, the WHO published growth charts based on the growth of breastfed babies and recommends this lower plane of growth as the optimum standard for growth of all infants [15, 16]. While the benefits of breastfeeding are well recognised, the 2010 UK Infant Feeding Survey showed that only 21 % of babies were exclusively breastfed at age 6 weeks and 1 % at 6 months [17]. Hence in addition to supporting breastfeeding, it is important to optimise the growth of formula-fed babies.

In the *Baby Milk* trial we aim to evaluate the efficacy, cost-effectiveness and acceptability of a theory-based, multi-component intervention to reduce formula-milk intake (based on the 2004 WHO recommendations for energy requirements) and prevent excess weight gain during infancy. We also aim to understand the psychological mediators of any effect of the intervention on formula-milk and energy intake.

## Methods/Design

### Study design

The *Baby Milk* trial is an explanatory, parallel, individually randomised controlled trial of parents (mainly mothers) and their babies who are formula-fed. The focus of the primary outcome measurement is the baby, but the focus of the intervention is the caregiver. The intervention will commence when the baby is enrolled in the study (between 2 and 14 weeks) and be delivered up to 6 months. Babies will be followed up to age 1 year. In this explanatory trial, the intervention programme will be delivered by trained and quality-assured facilitators (research nurses). Participants in the control group will be offered the same number of contacts and standard advice about formula feeding, and weaning will be discussed.

Ethical approval has been obtained from the Cambridgeshire 4 Research Ethics Committee (Ref:10/H0305/9), and fully informed written consent will be taken from all participants.

### Recruitment and retention

Parents and their babies who are partially or fully formula-feeding within 14 weeks of birth will be identified by research staff on a postnatal hospital ward; health professionals, including GPs, midwives and health visitors; and via a mail-out using the National Health Service (NHS) database (SystmOne). Most babies in England are delivered in the hospital and looked after by a community midwife for the first 2 weeks after discharge from hospital. Subsequently, they come under the care of a health visitor who records if they are formula-feeding in the NHS database. This database will be used to send a participant information sheet to parents in the catchment area. Research staff and midwives will identify babies within 2 weeks of birth. General Practices (GP, nurse, and other practice staff) will invite participants at the baby’s 6-week health check and immunisation clinics. Parents who return a reply slip expressing an interest in taking part or finding out more about the study will be contacted by research staff at the Medical Research Council (MRC) Epidemiology Unit to answer any questions, check eligibility criteria, and where appropriate, invite them for their baseline visit (at 2 to 14 weeks age). GPs and health visitors will be informed by letter if a baby under their care has been recruited into the study.

Maximising retention is an important issue and regular (4 to 6 weekly) contacts with participants in both groups should reduce attrition. The information sheet will emphasise the importance of follow-up irrespective of group allocation and adherence to the intervention. Participants who drop out from the intervention will be encouraged to attend for outcome measurements. For participants who withdraw from the trial, any data collected up to the withdrawal date will be retained and safely stored, but contact details will be removed.

### Inclusion and exclusion criteria

All healthy, term infants who are receiving formula-milk within 14 weeks of birth will be eligible to participate. We will exclude low birth weight (<2,500 g) and pre-term infants (<37 weeks gestation) and infants with major malformations, hormonal or metabolic diseases that might interfere with nutrition or growth. Infants who are on special formulas (soya-based, lactose-free, hydrolysed or anti-reflux formulas) at the time of recruitment will also be excluded; however, they will not be excluded if they are put on a special formula after randomisation.

### Measurements

A summary of the measurements undertaken is presented in Table 1.

**Table 1 Tab1:** Study measures

Measures	Baseline	4 months	6 months	8 months	12 months
Questionnaire measures					
Baseline questionnaire^a^	I, C				
Milk feeds questionnaire	I, C	I, C	I, C		
Maternal attitudes^b^	I, C		I, C		
Temperament, sleep and eating behaviour^c^			I, C		
4-day diet diary^d^				I, C	
Health Service Utilisation			I,C		I, C
Maternal quality of life^e^	I, C		I,C		I,C
Maternal anxiety^f^	I, C		I,C		
Intervention evaluation			I		I
Anthropometry					
Parents’ height	I, C				
Parents’ weight	I, C		I, C		I, C
Baby weight	I, C	I	I, C		I, C
Baby supine length	I, C	I	I, C		I, C
Baby head circumference	I, C		I, C		I, C
Baby abdominal circumference	I, C		I, C		I, C
Baby skin fold thickness					I, C
Baby abdominal Ultrasound					I, C

*I* Intervention group; *C* Control group

^a^Baseline Questionnaire: Parents: Demography (age; education - age at completion and highest qualification; occupation; ethnicity; marital status - cohabiting/married/single); weight and height. Mother’s: lifestyle (smoking - during pregnancy, current alcohol consumption), pregnancy (duration, weight -before pregnancy and at time of delivery), delivery (normal, instrumental, or caesarean) and previous children (number, feeding-breast, formula, dependent on instructions/appetite/growth - Likert scale). Baby’s: sex, weight and length at birth and 6 weeks

^b^Maternal attitudes and feeding practices (questionnaire developed for use in this study): Mother’s attitudes; psychological measures based on Social Cognitive Theory (self-efficacy, outcome expectancy, intentions, and motivation); perception of baby’s weight. Type of feed (breast/ expressed/ formula/ mixed), feed on demand/routine/both; feed based on instructions/appetite/growth – Likert scale

Bottle feeds (type, frequency, amounts, duration, how reconstituted, advice followed, age when started), Breastfeeds (frequency, duration, and expressed milk). Other drinks and foods. Age at weaning (only at 6 months)

^c^Validated questionnaires used with permission from [name] and [name]

^d^Diet diary: developed in collaboration with MRC HNR, and used in the National Diet and Nutrition Survey of Infants and Young Children

^e^Quality of Life: EuroQol Visual Analogue Scale and Short Form 8

^f^Anxiety: Spiegelberger Short State Anxiety Inventory

#### Anthropometry

Anthropometry data will be collected by trained research assistants using standard operating procedures. In order to minimise bias, the measurement team will be blind to group allocation and will be trained to avoid discussing this with parents. Parents will also be advised not to discuss allocation with the measurement team.

Weight will be measured with the baby undressed, using Seca Infant Electronic Scales™ and recorded to the nearest 0.01 kg. For supine length, the baby will placed on a Kiddimeter™ or Starters mat™, with only the nappy on and measured to the nearest 0.5 cm. Abdominal waist circumference will be measured using a D-loop non-stretch fibreglass tape measure and head circumference will be measured using the Child Growth Foundation reusable tape. Sub-scapular, triceps, quadriceps and flank skin fold thickness will be measured using the Holtain Tanner™/Whitehouse™ skin fold calliper with an average of three measurements taken for each site. A standard ultrasound device with a 3C-RS curved transducer will be used to measure intra-abdominal depth and subcutaneous fat.

Parents’ weight and percentage body fat will be measured on a Tanita™ scale and height with a Seca™ wall-mounted stadiometer.

#### Questionnaires

A baseline questionnaire will be used to collect data from parents about demography (age, education, occupation, ethnicity, marital status), lifestyle (smoking, alcohol consumption, BMI), pregnancy (duration, weight gain), delivery and previous children (number, feeding).

We have developed and validated a questionnaire to assess milk feeding practices and hypothesised psychological mediators of any intervention effect informed by Social Cognitive Theory: attitudes, self-efficacy, outcome-expectancies and intentions with regard to following feeding recommendation (feeding and growth questionnaire) [18]. Baby eating behaviour, sleep and temperament have recently been studied as potential risk factors for obesity [19–21]. We will use a combination of questionnaires developed by other groups ([name] and [name]) to assess these. The temperament questionnaire has been validated for use in infants [22] and the eating behaviour questionnaire has been validated in older children [23, 24].

A 4-day diet diary will be used to assess energy intake at 8 months. The diary will be the same as that used by the MRC Human Nutrition Research Unit (MRC HNR) for the National Diet and Nutrition Survey of Infants and Young Children (DNSIYC). Dietary data will be analysed using the Diet in Nutrients Out (DINO) computer package [25] by the dietary assessment team at the MRC HNR, who will not be aware of group allocation.

Parent’s quality of life will be assessed using the EuroQoL Visual Analogue Scale (VAS) and Standard Form (SF) 8. A questionnaire to measure health service utilisation (hospital, primary and community care use) using standard questions will be administered at 6 and 12 months. Parents’ perceptions of the usefulness of the different components of the intervention (face-to-face and telephone contacts, leaflets, stickers) will be assessed among intervention group participants.

The questionnaires will be self-administered prior to the visit with an opportunity to clarify any doubts during the visit.

### Randomisation and consent

Only participants who attend for the baseline visit will be randomised to intervention or control groups in order to minimise the bias from selective drop out. Central telephone randomisation will be conducted based on a random number table (generated by an independent statistician) linked to the study database. We expect that important covariates (such as birth weight, sex, gestational age, family size, maternal BMI, smoking, ethnicity, educational level, age at entry into the study and whether predominantly formula-fed) will be balanced between groups due to the large sample size. Written informed consent will be obtained at baseline visit by a trained research assistant conducting measurements.

### Intervention group

The MRC guidance for complex interventions was used to design the intervention [26]. This was an iterative process including a review of relevant theory to underpin the intervention; systematic reviews of parents’ experiences of bottle feeding [27] and determinants of non-recommended feeding practices [28]; and involvement of mothers, psychologists, doctors, midwives and health visitors [29]. The motivational component of the intervention is based on Bandura’s Social-Cognitive Theory (SCT), which has shown utility for understanding and changing dietary behaviours [30–32]. In order to help participants to translate their motivation into action, participants are encouraged to set goals and to formulate action plans, based on the concept of ‘implementation intentions’ [33–35]. They are also encouraged to monitor on a feeding-plan how much they are feeding their baby against *Baby Milk* intervention guideline amounts. Finally, participants are encouraged to keep on track by formulating coping plans (that is, problem solving), which are ‘if-then’ plans specifying how they will deal with difficult situations, such as the baby crying. In summary, the intervention consists of three components: a motivational component, an action planning component to help translate motivation into action (including goal setting, action plans and self-monitoring), and a coping planning component helping parents to deal with difficult situations.

The intervention will be delivered by trained facilitators (research nurses) from the baby’s enrolment in the trial (2 to 14 weeks old) to 6 months and will consist of three face-to-face sessions and two telephone contacts in addition to two leaflets based on SCT (Fig. 1). The face-to-face sessions will last approximately 30 to 45 min and the telephone contacts 15 to 20 min. Since social support is important, both parents will be encouraged to attend the face-to-face sessions. During the first session, the facilitator will talk parents through the ‘healthy infant growth and nutrition’ leaflet that explains the new feeding recommendations (Table 2) and the growth charts. The leaflet does not just impart knowledge about amounts of formula-feeds, hunger cues, growth charts and rapid weight gain, but also aims to encourage recommended feeding behaviours by strengthening self-efficacy and perceived benefits about following the recommendations. Demonstration of correct feed preparation (if required) and explanation of the feeding recommendations will be provided. Parents will be encouraged to make a feeding plan and provided with stickers to put on the formula milk packets. When the baby is 4-months old, parents will be invited for a second session and advice on weaning and feedback on baby’s growth will be provided. Two phone-calls - when the baby is age 2 to 3 months and 5 months - will be made to monitor progress with following recommendations and to support the parents with ongoing goal setting, action planning, self-monitoring and problem-solving. At the 6-month visit, the baby’s growth will be plotted on the WHO growth charts. Facilitators will feed back this information to parents, and they will be encouraged to monitor the growth of their babies also after the end of the intervention delivery at 6 months. Growth monitoring is important because parents are not very good at identifying obesity in their children [36], so any programme to prevent obesity must include early identification.

**Fig. 1 Fig1:**
[figure not shown]
Trial Flow Chart

**Table 2 Tab2:** Comparison between the guidelines on a standard formula milk packet and *Baby Milk* intervention guidelines

		SMA guidelines		Intervention guidelines		
Age	Weight	scoops/day	kJ/kg/day	scoops/day	kJ/kg/day	% Reduction
Birth	3.5 kg	18	496	18	496	0
2 wks	3.9 kg	24	590	18	442	25
1 mo	4.4 kg	24	525	21	459	13
2 mo	5.3 kg	25	454	22	399	12
3 mo	6.1 kg	25	393	22	346	12
4 mo	6.8 kg	35	494	30	423	14
6 mo	7.8 kg	32	390	28	341	13

Based on SMA™ white: 4.4 g/scoop; 2,173 kJ per 100 g powder

### Control group

The control group will be offered the same number of contacts with facilitators (attention control) and general information about formula-feeding (bottles, teats, sterilisation, making up feeds) will be discussed. The 4 to 6 weekly phone calls will be used to discuss general issues (parenting, sleep, etcetera), to monitor feed quantity and frequency and to encourage continued participation in the study.

Parents in both groups will be given a help-line number to contact the study team about feeding issues.

### Training in intervention delivery and intervention fidelity

Facilitator training includes a 2-day training programme in the evidence base underlying the intervention, theories, behaviour change techniques, intervention strategies and communication skills, including demonstration and practice with individual feedback. The training is supported by an extensive training manual. In order to standardise intervention delivery, facilitators will use standardised protocols for all the contacts in the intervention and control conditions. Four research nurses will deliver the intervention and control group protocols and all face-to-face and telephone consultations will be audio-taped. Fidelity will be promoted, and contamination across the two groups minimised by assessing a random sample of audio-taped contacts using standardised fidelity checklists, peer appraisal, followed by feedback and team discussion. Team meetings will be held over the whole period of intervention delivery to discuss and problem solve challenging situations.

### Sample size calculation

The primary outcome is conditional infant weight gain from birth to 12 months of age (conditional on birth weight). Birth weight and weight at 6 and 12 months will be converted to standard deviation scores (SDS) adjusted for age and sex using the WHO 2006 growth standard. SDS refers to the number of standard deviations the measurement lies above (positive value) or below (negative value) the 50^th^ percentile (median value 0). Conditional weight gain is calculated as the change in weight SDS between birth to age 12 months, adjusted for birth weight SDS.

In the Avon Longitudinal Study of Parents and Children (ALSPAC), among 518 formula and mixed-fed infants, mean ± SD for conditional weight gain was 0.65 ± 0.87, and for energy intake at 4 months was 2768 ± 479 kJ/day. Based on those data, we estimated that our target 15 % (420 kJ/day) reduction in energy intake would lead to a (mean ± SE) 0.16 ± 0.04 lower gain in weight SDS between 0 to 8 months [37]. We have powered the study on a more conservative estimate of a 10 % to 11 % achieved reduction in energy intake, which corresponds to a difference in weight SDS of 0.11 to 0.12. However, the estimated effect size should be corrected for regression dilution because energy intake in ALSPAC was estimated from unweighed 1-day diet diaries. Lanigan et al. reported the within- (778 kJ) and between-infant (824 kJ) SD during the 5-day diet diaries in the 6- to 24-month-old infants, and this gives a regression dilution correction factor of 1.89 [38]. With a 10 % to 11 % lower calorie intake in the intervention group, we can expect a 0.20 to 0.21 SDS (0.11 to 0.12*1.89) difference between the two groups.

Sample sizes of 250 to 290 infants in each group will provide 80 % power at the two sided 5 % level to detect a 0.20 to 0.21 SDS difference in weight gain between the intervention and the control group. Allowing for around 15 % loss to follow-up, we aim to recruit 300 to 350 infants to each group.

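### The expected effect (0.20 to 0.21 SDS), its stated product and the lower sample size of 250 per group do not agree: 250 gives about 77% power at 0.21 SDS, and the recruitment floor differs between abstract and text

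*Protocol article*

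**What the plan says.** All the inputs stand in the protocol article under Sample size calculation.

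- **Variability.** In the cohort of formula-fed and mixed-fed infants used for planning, "mean ± SD for conditional weight gain was 0.65 ± 0.87". No other SD is given.
- **Effect before correction.** A 15% cut in energy intake is taken to lower weight gain by 0.16 SDS (SE 0.04). The trial is powered on a 10% to 11% cut, stated as 0.11 to 0.12 SDS.
- **Effect after correction.** A regression dilution factor of 1.89 is applied, and "we can expect a 0.20 to 0.21 SDS (0.11 to 0.12*1.89) difference between the two groups".
- **Sample size.** "Sample sizes of 250 to 290 infants in each group will provide 80 % power at the two sided 5 % level" for that difference.
- **Recruitment.** After about 15% loss to follow-up, "we aim to recruit 300 to 350 infants to each group", which is 600 to 700 in total. The Methods/Design part of the abstract says: "We will recruit 650 to 700 parents".

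**The concern.** The effect, its derivation, the sample size and the recruitment target form one chain, and each link can be checked against the one before. Two links fail. The printed product does not equal its printed factors, and the lower sample size does not give the stated power for either printed effect. The recruitment floor in the sample size section appears to be 250 inflated for loss, so any error in the 250 or in its paired effect carries into the target. The abstract then gives a different floor.

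This is the justification for the primary outcome, and the article reports that the trial was recruiting at submission. A reader cannot tell which difference the lower end of the plan was meant to detect, or which total counts as reaching the target.

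**Working it through.** **Inputs** (protocol article, Sample size calculation): SD 0.87; two-sided 5%; 80% power; equal groups; loss 15%; effects and group sizes as above. Normal approximation for two means.

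**1. Dilution factor.** 1 + (778/824)² = 1.891. The stated 1.89 reproduces.

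**2. Corrected effect.**
- From the printed factors: 0.11 × 1.89 = 0.208; 0.12 × 1.89 = 0.227.
- From the unrounded inputs: 0.16 × 10/15 × 1.89 = 0.202; 0.16 × 11/15 × 1.89 = 0.222.

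The unrounded route reproduces the printed lower value of 0.20. Neither route gives 0.21 as the upper value.

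**3. Required size per group.** n = 2 × (1.960 + 0.8416)² × 0.87² / d² = 11.88 / d².

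| Difference d (SDS) | Source | n per group |
|---|---|---|
| 0.20 | printed, lower | 298 |
| 0.202 | unrounded, 10% cut | 293 |
| 0.21 | printed, upper | 270 |
| 0.222 | unrounded, 11% cut | 242 |

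The printed 290 is close to the need at 0.20 to 0.202. The printed 250 is 20 below the need at 0.21, but slightly above the need at 0.222. Rounding of the effect does not rescue 0.21: even at 0.215, n = 11.88 / 0.0462 = 257.

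**4. Power at the printed sizes.** Power ≈ Φ(d / (0.87 × √(2/n)) − 1.960).
- 290 at 0.20: 0.20 / 0.0722 − 1.960 = 0.81, power 79.1%.
- 250 at 0.21: 0.21 / 0.0778 − 1.960 = 0.74, power 77.0%.
- 250 at 0.22: power 80.7%.

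The two-sample t-test gives almost the same: 78.9% for 290 at 0.20 and 76.8% for 250 at 0.21. The difference detectable with 80% power is √(11.88/250) = 0.218 at 250 per group and √(11.88/290) = 0.202 at 290.

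**5. Loss to follow-up.** 250/0.85 = 294 and 290/0.85 = 341, so 300 and 350 are sensible upward roundings of the printed sizes. This step is sound in itself.

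**6. Power across the two recruitment ranges, after 15% loss.**

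| Total recruited | Evaluable per group | Power at 0.20 | Power at 0.21 | Power at 0.22 |
|---|---|---|---|---|
| 600 (sample size section, floor) | 255 | 74% | 78% | 81% |
| 650 (abstract, floor) | 276 | 77% | 81% | 84% |
| 700 (both, ceiling) | about 297 | 80% | 84% | – |

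The 0.22 entries use the formula of step 4: 0.22/0.0770 − 1.960 = 0.90 gives 81%, and 0.22/0.0740 − 1.960 = 1.01 gives 84%.

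**The case against.** **The group sizes may be right and only the printed 0.21 wrong.** This is the strongest defence, and it largely stands. The unrounded effects of 0.202 and 0.222 need 293 and 242 per group, close to 290 and 250. Scaling by the stated 420 kJ/day instead gives the same picture: an 11% cut is 0.11 × 2768 = 304.5 kJ, so 304.5/420 × 0.16 × 1.89 = 0.219 SDS and n is about 247. It follows that 250 should not be called too small without qualification. The text still cannot stand as printed, because it attaches 80% power to 0.21.

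**A reader might infer that power falls to 73%.** That figure (72.9%) comes from setting the smallest group against the smallest effect, 250 at 0.20. The text does not spell out the pairing, but in a statement of two ranges the larger size belongs with the smaller effect. Read so, only one end falls short, by about 3 points.

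**Covariate adjustment could close the gap.** For 250 per group to have 80% power at 0.21, the residual SD need only be 0.838, that is 1 − (0.838/0.87)² = 7% of variance explained. The data analysis section does plan further covariates. But 0.87 is already the SD of conditional gain, and the article states no further reduction, so this is an assumption and not a reconciliation. Nor does a single SD fit both printed pairs: 290 at 0.20 implies 0.860, and 250 at 0.21 implies 0.838.

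**The discrepancy is small beside the uncertainty of the source effect.** With 0.16 and SE 0.04, the corrected effect at the 15% target spans about 0.15 to 0.45 SDS at 95% ((0.16 ± 1.96 × 0.04) × 1.89). This is fair, and it limits the weight of the point.

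**The recruitment ranges overlap.** They do: 650 to 700 lies wholly inside 600 to 700, and the ceiling is the same. A reader might infer that the plan permits stopping at 600, but nothing in the article says so. What remains is a difference between two stated floors.

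**Conclusion.** Wrong as written, of minor to moderate weight. The printed effect range, its product with 1.89 and the lower sample size cannot all be correct together. At the printed 0.21 SDS, 250 per group has about 77% power instead of 80%; the 290 end is acceptable at about 79% for 0.20 SDS. The upper effect of 0.21 is the likelier slip, since about 0.22 follows from the article's own inputs and 250 then gives about 81%. The two recruitment floors, 600 and 650, lie on either side of 80% power for 0.21 SDS (about 78% and 81%).

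This rests on SD 0.87, equal groups, a simple comparison of two means, 15% loss, and the pairing of 290 with 0.20 and 250 with 0.21. It does not show that the trial as a whole is under-powered: the common ceiling of 700 gives 80% even at 0.20 SDS. Design, primary outcome and analysis are untouched.

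**What to change.** Choose one of two coherent restatements. Applying parts of both, with a larger effect and also larger groups, would leave the section inconsistent again.

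- **(a) Correct the effect.** Give the expected difference as about 0.20 to 0.22 SDS, show the unrounded product (0.202 to 0.222), and state that 290 and 250 evaluable infants per group give about 80% power at about 0.20 and 0.22 SDS respectively.
- **(b) Keep 0.20 to 0.21 SDS.** Restate the requirement as 298 to 270 evaluable per group, about 351 to 318 recruited per group at 15% loss (702 to 636 in total). Alternatively, keep 250 and state 77% power at 0.21. The bracketed product must still be corrected or replaced by the actual basis for 0.21.

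In either case, give the same total recruitment range in the abstract and in the sample size section, and state the power at its floor: for 0.21 SDS after 15% loss, about 78% at 600 and 81% at 650. Under (a), add the figure for 0.22 SDS, which is about 81% at 600.

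The cost is wording only. The ceiling stays at 700, apart from two infants under a strict reading of (b), where 700 already gives 80.1% at 0.20 SDS. If 250 is kept against 0.21 SDS, the stated power becomes slightly less favourable.
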